### Blinding

Data collectors and analysts will be blinded to trial allocation following initial randomization. Data analysts will become unblinded following analysis of the primary outcome for reporting purposes. All trial participants will receive an invitation to screen for free as part of a large male health study, but will remain blinded to the use of varying invitational techniques across trial conditions.

### Statistical analyses

#### Primary outcome

A 2 x 4 (participation by intervention group) chi-squared test with alpha set at 0.05 will compare FIT participation rates between groups. Potential covariates such as demographic factors (age and socioeconomic status) and psychosocial variables (survey sample only) will be checked by the change in coefficient method using log binomial generalized linear models.

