Consistent with a number of international screening programs [32], the NBCSP invites participants to screen by the use of mailed invitation letters accompanied by a free fecal immunochemical test (FIT) [7]. A FIT is a type of FOBT that does not require dietary restrictions prior to its use [33]. The current invitation protocol for the NBCSP operates along a framework consistent with the TTM. First, participants are mailed an advance notification letter informing them that within 2 weeks they will receive a screening package. The aim of the advance notification is to encourage movement from precontemplation (not yet thinking about screening) to contemplation (thinking about screening) [34]. The subsequent invitation letter and associated screening package then seeks to shift these participants from contemplation (theoretically achieved by the advance notification) to the action stage; completing the FOBT. Although this contact schedule is consistent with the TTM staging framework, the content of the letters is not tailored according to the stage that each letter is designed to target. Including messages that target psychosocial variables relevant to men in these stages has the potential to encourage stage progression and improve screening uptake. Specifically, perceived barriers, social influence and social support all operate at the early stages of readiness, and should be emphasized in advance notification letters; while perceived benefits and self-efficacy operate at the later stages of readiness, and are best addressed in communication aimed at invitation [29-31].

The objectives of this study are to determine: 1) whether invitational strategies that target male attitudes toward screening, and matched to stage of readiness to screen, enhance FOBT participation compared to a standard approach; 2) which combination of targeted and standard materials are most effective in enhancing participation; and 3) whether targeted invitational strategies lead to change in psychosocial variables related to male screening participation. This study will also explore men’s reactions to, and evaluation/acceptance of, the invitations.

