## Methods

### Study design

This study is a factorial design, RCT. A national sample of Australian men aged 50 to 74 years inclusive, will receive a free, mail delivered FIT, accompanied by either standard invitational materials (control), invitational materials modified to target psychosocial variables associated with stage of readiness to screen, or a combination of the standard and modified materials. The intervention will offer screening to participants consistent with the protocol utilized by the NBCSP, which includes a mailed advance notification letter, followed 2 weeks later by a mailed invitation letter and screening package. The content of the advance notification and invitation letters will differ by trial arm. The letters currently utilized by the NBCSP will serve as the control. The modified advance notification letter will be designed to target men in the precontemplation stage, while the modified invitation letter will target men in the contemplation stage.

Participants will be randomized to one of four trial arms of equal size (allocation ratio 1:1:1:1). Within each trial arm, participants will be randomized to a survey group, or a screening only group (allocation ratio 1:2.83). Participants in the survey group will complete behavioral surveys measuring the psychosocial variables targeted in the intervention, before commencing the screening phase (baseline) and again upon its completion (endpoint). Participants in the screening only group will receive the screening offer, without prior study engagement, consistent with the NBCSP. The use of behavioral surveys pre- and post-intervention will allow the study to examine the impact of the letters on the psychosocial variables they are designed to target. However, survey participation will be restricted to a survey subgroup because of the potential for completion of the survey to lead to increased screening awareness for this population.

Upon completion of the screening phase, a purposively selected subsample of participants in the screening only group will be invited to participate in semi-structured interviews to evaluate the intervention. The study design flow chart is shown in Figure 1.

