### Intervention (screening phase)

The intervention involves four arms: 1) standard advance notification letter and standard invitation letter consistent with the NBCSP (control); 2) targeted advance notification letter plus standard invitation letter (T1); 3) standard advance notification letter plus targeted invitation letter (T2); and 4) targeted advance notification letter and targeted invitation letter (T3).

Screening will be offered to all baseline survey respondents and participants in the screening only groups according to the schedule described in Table 2.

**Table 2 T2:** Screening schedule

**Week**	**Study process**
Week 1	Mailed advance notification
Week 3	Mailed invitation and screening package
Week 9	Mailed reminder letter to non-respondents
Week 15	Cease data collection

Screening packages will include: 1) two-sample FIT (OC-Sensor, Eiken Chemical Co, Tokyo, Japan); 2) screening invitation letter; 3) FIT instruction leaflet; 4) CRC and screening information booklet; 5) participant details and consent form; and 6) reply paid envelope. Those who do not participate in the FIT screening offer within the first 6 weeks will receive a standard reminder letter irrespective of trial allocation. Consent to participate in the screening will be obtained via return of the completed participant details and consent form, and/or return of the completed FIT.

It is anticipated that some participants invited to screen will already be up to date with screening or may not be suitable for screening due to current medical conditions (for example chronic bowel conditions and past CRC diagnosis [40]). Consistent with the NBCSP, participants will be encouraged to first discuss screening with their general practitioner and to then contact the research team if screening is not required. Reasons for non-participation (for example up to date with screening, medical reason and no reason provided) will be recorded for analysis. A screening withdrawal form, where invitees can provide reasons for non-participation, will be included in the screening information booklet to assist with this process, along with telephone and email contact information.

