### Sample size considerations

Assuming a 50% return of the baseline survey, screening will be offered to a total of 8,000 participants (1,200 survey participants and 6,800 screening only participants). Participants who contact the research team and opt-out of screening due to: 1) recent FOBT screening; 2) recent colonoscopy; 3) recent bowel cancer diagnosis; or 4) medical condition that prevents the use of FOB-based screening tests, will be excluded from analysis on the basis that screening is not suitable/required for this group [3]. Those who opt-out of screening for reasons other than those listed previously (for example did not want to complete the screening) will be categorized as a non-participant for the purpose of analyses. Survey group participants who opt-out of the study prior to completing the endpoint phase will be excluded from analyses involving survey data.

Two participation rates will then be calculated for each trial arm: 1) inclusive of survey participants (2,000 per trial arm); and 2) exclusive of survey participants (1,700 per trial arm). Analyses will be conducted both with and without the inclusion of survey participants because participation for this subgroup is likely to be higher due to the baseline survey acting as a prompt for screening participation. Assuming a participation rate of at least 40% for the control group and allowing for up to 40% of invited participants to be excluded due to being up to date with screening [8], these group sizes permit the detection of differential FOBT uptake of at least 6% between any two groups with at least 80% power. A difference of at least 6% was considered by the research team to be the smallest difference that would be feasible to detect without requiring overly large sample sizes, and is similar to the effect size estimate used in our previous research [36].

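### The 2 x 2 factorial trial has one 3-df chi-squared test as its stated primary analysis, so objectives 1 and 2 have no matching test of letter effects, interaction or arm-versus-control contrasts

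*Protocol article*

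**What the plan says.** The Study design section states: "This study is a factorial design, RCT". The Intervention section lists the four arms. Control has both letters standard, T1 has only the advance notification targeted, T2 has only the invitation targeted, and T3 has both targeted. Allocation is 1:1:1:1. This is a complete 2 x 2 crossing.

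The end of the Background gives the objectives. The first asks whether targeted strategies raise participation over the standard approach. The second asks "which combination of targeted and standard materials are most effective in enhancing participation".

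Under Statistical analyses, Primary outcome, the test is: "A 2 x 4 (participation by intervention group) chi-squared test with alpha set at 0.05 will compare FIT participation rates between groups". The only model named there is for covariates, which "will be checked by the change in coefficient method using log binomial generalized linear models". No letter effect, interaction or contrast between arms is named.

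Under Sample size considerations the inputs begin: "Assuming a participation rate of at least 40% for the control group". The claim is that "these group sizes permit the detection of differential FOBT uptake of at least 6% between any two groups with at least 80% power". Participation rates are to be calculated per arm, once with and once without the survey participants, and neither set is named as the main one.

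**The concern.** A 2 x 4 chi-squared test treats the arms as four unordered groups and has three degrees of freedom. A significant result says that at least one rate differs from the others. It does not say whether targeting helps or harms, which letter is responsible, whether the letters act together, or how any targeted arm compares with control. Those are the questions that objectives 1 and 2 raise.

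The sections also do not line up. The design is factorial, the sample size is set for a pair of arms, and the test is global across four arms. The pair that is powered is not a listed test, and neither section uses the comparison that a factorial layout makes available, two arms against two arms for each letter.

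What is at stake is mainly interpretation. Unless contrasts are fixed beforehand, the effective letter or combination would be picked after the rates have been seen.

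**Working it through.** **Inputs (Protocol article, Sample size considerations and Primary outcome).** Control rate 40%; target difference 6 points; up to 40% of invited men excluded; 2,000 per arm with survey participants and 1,700 without; alpha 0.05. I take the tests as two-sided, since sidedness is not stated.

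Analysable men per arm: 2,000 x 0.6 = 1,200 and 1,700 x 0.6 = 1,020.

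**1. The plan's own figure.** For two groups of size n with rates p1 and p2 and mean p, power = Φ{[|p2 − p1|√n − 1.96√(2p(1 − p))] / √(p1(1 − p1) + p2(1 − p2))}. For 40% v 46%:
- n = 1,200: 84.4%
- n = 1,020: 78.2%

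The stated 80% is reproduced to within 2 points, for a single uncorrected pair.

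**2. Detectable difference at 80% power from 40%.** Same formula, solved for p2. The per-letter comparison pools two arms on each side.

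| | 1,020 per arm | 1,200 per arm |
|---|---|---|
| One pair of arms | 6.1 points | 5.7 points |
| One letter, two arms v two arms | 4.3 points (2,040 v 2,040) | 4.0 points (2,400 v 2,400) |
| One letter, alpha 0.025 | 4.8 points | 4.4 points |

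**3. Power of the omnibus test against a letter's main effect.** The omnibus noncentrality is λ = n Σ(p_i − p̄)² / [p̄(1 − p̄)] on 3 df. Example: rates 40, 46, 40, 46% at 1,020 per arm give λ = 1,020 x 0.0036 / (0.43 x 0.57) = 14.98 and power 91.7%.

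| True pattern (control, T1, T2, T3) | Omnibus, 1,020 / 1,200 | Main effect of a letter, 1,020 / 1,200 |
|---|---|---|
| One letter +6, other 0 (40, 46, 40, 46%) | 91.7% / 95.5% | 97.2% / 98.8% |
| One letter +4, other 0 (40, 44, 40, 44%) | 56.9% / 64.7% | 73.5% / 80.2% |
| Only the combination works, +6 (40, 40, 40, 46%) | 81.7% / 88.0% | 49.4% / 55.9% |
| +3 from each letter (40, 43, 43, 46%) | 62.2% / 70.1% | 49.0% / 55.5% |

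In rows 1 and 2 the main effect is that of the working letter. In rows 3 and 4 each letter's margin is a 3-point difference (40.0 v 43.0% and 41.5 v 44.5%). With alpha split at 0.025 per letter, main-effect power in row 1 is 94.9% / 97.5%.

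**4. Interaction.** As a difference of differences, the detectable size at 80% power is 2.80 x √(4 x 0.43 x 0.57 / n) = 8.7 points at 1,020 per arm and 8.0 at 1,200.

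**The case against.** The strongest defence is that a four-arm comparison is a legitimate choice here. The Background describes a sequence in which the advance letter moves men to contemplation and the invitation then moves those men to action. That theory makes an interaction plausible, and main effects averaged over the other letter would then be hard to read. Objective 2 is itself a question about arms. Rates per arm will be reported, so direction and ranking will be visible, and the log binomial models may yield intervention coefficients. This is also a condensed article, and follow-up contrasts are often left to an analysis plan.

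Much of this stands. It means main effects should not simply replace the arm comparison, and table 3 above shows that they are not uniformly more powerful. It does not remove the mismatch. The article fixes a primary test and its alpha, and that test answers neither objective whatever is added later. Visible rates are not a prespecified contrast, and the models are introduced only for checking covariates.

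A reader might infer that the plan discards part of the sample, uses half the men for each letter, or analyses single arms. The documents do not support this. The chi-squared test uses every man in all four arms, and the analysis section lists no single-arm comparison. The phrase about any two groups belongs to the sample size section.

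**Conclusion.** The point holds. The stated primary analysis does not match the factorial design or the first two objectives, and the powered comparison is not among the listed tests. This should be fixed, but it does not make the trial or its stated test invalid.

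The gain in precision is conditional. If the letters do not interact, each letter's detectable difference falls from 6.1 or 5.7 points for one pair of arms to 4.3 or 4.0. If one letter adds 6 points, power is 97% or 99% for its main effect against 92% or 96% for the omnibus test. The order reverses when only the combined letters work (49% or 56% against 82% or 88%) and when each letter adds 3 points (49% or 56% against 62% or 70%). It would therefore be wrong to infer that the factorial analysis is always the more powerful one. The case rests on answering the stated questions, with precision as a benefit under approximate additivity.

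These figures assume a 40% control rate, the full 40% exclusion and two-sided tests at 0.05.

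**What to change.** - Prespecify a binomial model (log binomial, or with an identity link for risk differences) with targeted advance letter, targeted invitation and their interaction. Define each letter's main effect as the average over the two levels of the other letter, so that it is not confused with a simple effect.
- Report a risk difference and risk ratio with 95% CI for each letter, and the interaction with its CI.
- Report the three arm-versus-control differences with CIs beside the main effects. They serve objective 2 and protect the reading if the letters interact.
- State a multiplicity rule, for example 0.025 per letter, and say what status the arm contrasts have under it.
- Name which of the two populations, with or without survey participants, is the main one.
- Keep the 2 x 4 chi-squared test as the global or supportive test.
- Align the sample size text with the comparison that is finally named as primary.

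**Cost.** No new men or data are needed, and the model family is already named. It does need a dated amendment: Trial status says the screening phase ended in June 2013, and Blinding says analysts are unblinded after the primary outcome is analysed, so the change must be recorded before then. Splitting alpha raises the per-letter detectable difference to 4.8 or 4.4 points. An interaction below about 8 to 9 points would probably go undetected, so a non-significant interaction must not be read as proof of additivity.

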### Randomization

Trial participants will be randomly sorted according to an assigned random integer from 1 through n (total eligible sample). Subsequently, block randomization will be performed using random allocation software [35] with the four trial conditions specified, and with random block sizes of 4, 8 and 12. Participants will then be assigned to trial conditions according to the randomly assigned integer and its corresponding trial condition specified in the block randomization output. Following allocation to trial conditions, participants will be assigned a random integer from 1 through n within each condition, and those assigned integers 1 through 600 in each condition will be assigned to the survey group for the corresponding trial arm. Randomization will be performed by a member of the research team (not the primary investigator) using de-identified data (participant names will be replaced by a numerical study identification number).

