#### Secondary outcomes

Change in psychosocial variables from baseline to endpoint will be calculated for the participants who complete both surveys. Change scores will be calculated by subtracting baseline from endpoint scores for each of the variables targeted by the intervention. These change scores will then be compared between intervention groups using analysis of covariance (ANCOVA), controlling for potential co-variation from demographic variables. Based on the predicted group sizes mentioned above, the ANCOVA using two-tailed significance will have 80% power to detect a difference of at least half a standard deviation for psychosocial variables between any two groups.

Qualitative data collected via telephone interviews will be analyzed using the framework analysis method recommended for applied health research by Green and Thorogood [45]. This method is suited to applied health research as it allows for the exploration of themes derived from *a priori* aims relevant to this research stage as well as emergent themes raised by respondents. The study will aim to recruit 20 screening participants and 20 non-participants for interview in order to achieve data saturation [45].

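### Covariates for the supplementary adjusted participation models are chosen by change in coefficient, so the model depends on chance imbalance, the observed effect and an unstated cut-off; fix the set in advance.

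*Protocol article*

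**What the plan says.** Under Statistical analyses, Primary outcome, the main comparison is unadjusted: "A 2 x 4 (participation by intervention group) chi-squared test with alpha set at 0.05 will compare FIT participation rates between groups". The same paragraph adds a second step. The candidates are "Potential covariates such as demographic factors (age and socioeconomic status) and psychosocial variables (survey sample only"), and they "will be checked by the change in coefficient method using log binomial generalized linear models". The list is illustrative rather than closed, and the size of change that counts is not given.

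Allocation is random. Study design states: "Participants will be randomized to one of four trial arms of equal size (allocation ratio 1:1:1:1"). Randomization describes blocks "with the four trial conditions specified, and with random block sizes of 4, 8 and 12", and mentions no stratification of the allocation by age or socioeconomic status.

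Under Secondary outcomes, change scores on the psychosocial variables are compared by ANCOVA, "controlling for potential co-variation from demographic variables". The baseline score is not among the covariates described there.

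**The concern.** Change in coefficient is a way of looking for confounders in observational data. In a randomised comparison no baseline covariate is systematically tied to arm, and a risk ratio from a log binomial model is collapsible, so adjusting for a balanced covariate leaves it where it was. What mostly moves it is chance imbalance. A covariate is adjusted for in trials where it happened to be unbalanced, or where the estimated effect happened to be small, and left out otherwise.

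At stake is the adjusted risk ratio and its interval. Two analysts with the same data and different cut-offs could report different models, and a covariate that predicts uptake may be left out when including it would help a little. Because this rule is written into the protocol, it is not a detail left to a later analysis plan.

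**Working it through.** **1. The plan's own figure.** Sample size considerations gives 2,000 per arm with survey participants and 1,700 without, a control rate of 40%, up to 40% excluded, and at least 80% power for 6 points. Analysed numbers are 2,000 × 0.6 = 1,200 and 1,700 × 0.6 = 1,020. Two-sided alpha is 0.05 and the rates are 40% and 46% (mean 43%):

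z = [0.06 − 1.96 × √(2 × 0.43 × 0.57 / n)] / √[(0.40 × 0.60 + 0.46 × 0.54) / n]

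- n = 1,200: (0.06 − 0.0396) / 0.0202 = 1.01, power 84.4%.
- n = 1,020: (0.06 − 0.0430) / 0.0219 = 0.78, power 78.2% (80.2% for 40% versus 34%).

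The claim is reproduced to within 2 points. It concerns the unadjusted comparison, so the covariate rule does not touch it.

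**2. How far a covariate can move the coefficient.** For a standardised covariate with log risk ratio b per SD, the shift is about b × (difference in arm means). With 1,200 per arm that difference has SD √(2/1,200) = 0.0408. I assume b = 0.1 to 0.2, because the document gives no value.

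- b = 0.1: shift SD 0.0041, median absolute shift 0.6745 × 0.0041 = 0.0028.
- b = 0.2: shift SD 0.0082, median absolute shift 0.0055.

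**3. How far it must move under a 10% rule (assumed threshold).**

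- No effect: the estimated log risk ratio has SE √(2 × 0.6 / (0.4 × 1,200)) = 0.050, so 10% of it has SD 0.0050, about the size of the shift itself. Treating the two as independent normal variables, the chance that one covariate is kept is 1 − (2/π) × arctan(0.0050 / shift SD), which is 44% at b = 0.1 and 65% at b = 0.2. Simulation agrees: the mean number kept out of two was 0.86 and 1.32, or 43% and 66% each.
- Planned effect: ln(0.46/0.40) = 0.140, and 10% of it is 0.0140. That is 0.0140/0.0041 = 3.4 shift SDs at b = 0.1 and 0.0140/0.0082 = 1.7 at b = 0.2, so selection becomes uncommon.

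**4. Simulation.** Two arms of 1,200, two prognostic covariates independent of arm, and a log-link modified Poisson model with robust SE, which has the same estimand as the log binomial model. Share of trials in which at least one covariate is kept (range over b = 0.1 to 0.2):

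| Threshold | No effect | 40% v 46% |
|---|---|---|
| 5% | 81-95% | 23-62% |
| 10% | 58-83% | 4-22% |
| 20% | 34-59% | 1-3% |

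Results at 1,020 per arm were similar. A separate simulation used a linear probability approximation, 1,020 per arm, covariates worth 8 and 5 points of uptake per SD, and a 10% rule. It kept them in 63% and 49% of null trials, and in 14% and 6% at 6 points.

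**5. Consequence for error rates.** Type I error of the selected model was about 4-6%. Power at 40% v 46% under the 10% rule:

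| n per arm, b | Unadjusted | Selected | Fixed set |
|---|---|---|---|
| 1,200, 0.1 | 85.3% | 85.4% | 86.1% |
| 1,200, 0.2 | 85.1% | 86.7% | 87.5% |
| 1,020, 0.1 | 77.7% | 78.0% | 77.8% |
| 1,020, 0.2 | 76.3% | 78.8% | 80.4% |

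The separate simulation gave type I error of 5.6% selected v 5.7% unadjusted, and power of 79.8% selected v 80.5% with a fixed set.

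**6. The ANCOVA.** If baseline and endpoint scores have equal variance σ² and correlation ρ, a change score has variance 2σ²(1 − ρ). With the baseline score as covariate the residual variance is σ²(1 − ρ²). The ratio is (1 + ρ)/2, below 1 for any ρ below 1. Adding the baseline score therefore improves on adjusting for demographics alone, unless those already carry the same information.

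**The case against.** The strongest reply is that little depends on this. The confirmatory test is unadjusted, type I error is not materially inflated, and the power gap between a selected and a fixed model is at most a couple of points in the runs above. The high retention rates with no effect arise largely because the shift is divided by a near-zero coefficient. All of this stands, and it limits the point to the supplementary estimate.

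Three further replies also have force:

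- A reader might infer that the rule ignores prognosis. It does not: the shift is imbalance times prognostic strength, and the stronger covariate was kept more often (63% v 49%; 14% v 6%).
- A reader might say that only chance can move the coefficient. That is too strong. Sample size considerations excludes men who opt out, after the letters, for listed screening or medical reasons, and the targeted advance letter encourages talking to a doctor, so those exclusions could differ by arm. Choosing covariates by coefficient shift is still no remedy for that.
- A reader might infer that the secondary results are also selected on the treatment effect, or that the ANCOVA covariates would be picked with arms known because "Data analysts will become unblinded following analysis of the primary outcome for reporting purposes". The document supports neither. The selection rule is tied to the log binomial models, the ANCOVA text states no selection rule, and Trial status gives data-collection dates but no date on which covariates are settled.

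Finally, the text says only that covariates are checked. Selection for adjustment is nevertheless the ordinary meaning of the named method.

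**Conclusion.** The point holds as a minor improvement. In this randomised comparison the stated rule makes the content of the adjusted participation model depend mainly on chance imbalance, the observed effect and a cut-off that is not given. With 1,200 per arm and a 10% rule, at least one of two covariates enters in roughly 58-83% of null trials and 4-22% at the planned effect. These figures rest on assumed covariate strengths (log risk ratio 0.1 to 0.2 per SD), two covariates, an assumed threshold and a single two-arm contrast. The direction does not depend on the exact values. The primary chi-squared test, its alpha and the stated power are unaffected. The cost is an adjusted estimate whose model cannot be known in advance, plus a small loss of precision. It is not a false-positive problem.

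**What to change.** - Keep the unadjusted chi-squared test as the primary analysis.
- Replace the change-in-coefficient step with one log binomial model whose covariates are fixed in advance on prognostic grounds: age, the socioeconomic measure that the protocol already names, state, and survey group where survey participants are included. Report it whatever the coefficient does.
- In the survey sample, state that only baseline psychosocial values may serve as covariates. The same variables are measured again at endpoint, after letters designed to change them. The protocol does not say that endpoint values would be used; the wording should simply rule it out.
- In the ANCOVA of change scores, add the baseline score of each psychosocial variable as a covariate.

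The cost is a change of wording and slightly more analysis work. One item needs checking. Participants describes the electoral-roll information as names and addresses, and the survey demographics cover only survey respondents (an expected 1,200 of 8,000 men offered screening). The source of socioeconomic status for screening-only men must therefore be confirmed before it is fixed as a covariate.
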